### Sample size calculation

We assume that about 15% of women in the control group will report feeling anxious (agree or strongly agree) or use health services (eg, general practitioner consultation or intend to undergo supplemental screening). Achieving 80% power to detect differences in proportions for the primary outcomes between each of the intervention arms and the control arm of ten percentage points (adjusted α = 0.013 for three pairwise comparisons) would require that 373 women in each study arm. We will also undertake longitudinal analyses, and assume 80% retention at eight weeks, 70% at twelve months, and 70% at 27 months. To maintain the overall sample size of 1119 women at 24 months, we aim to recruit 2856 women for the baseline (952 per arm). No further control of the family‐wise error rate was applied in our evidence‐generating real world study.

Based on the number of women screened at the BreastScreen Queensland Sunshine Coast services and a conservative estimate that 30% of screened women will have dense breasts,^39^ recruiting the desired target sample size will take about six months. A brief pilot phase (one week) will ensure that any problems are identified and resolved prior to the main RCT; if no changes to the study design are required, data for the pilot participants will be included in our analysis. If changes are needed, the pilot participant data will not be included, and an application to amend the ethics approval will be submitted.

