### Randomised controlled trial component of the study

Our prospective study will comprise an RCT to assess the effects of notifying women screened in the Australian population‐based breast screening program about dense breast findings, and a longitudinal qualitative sub‐study. Eligible women will be allocated in equal numbers to the three study arms using a random number generator without informing them of their allocation:
arm 1 (control group): standard BreastScreen Australia care (no notification about breast density);arm 2 (intervention group 1): notification about dense breasts in the screening results letter and written health literacy‐sensitive information; orarm 3 (intervention group 2): notification about dense breasts in the screening results letter and a link or QR code to online video‐format health literacy‐sensitive information (Box 1).

Box 1Overview of our investigation of the immediate and longer term effects of breast density notification for women undergoing routine breast screening at eight BreastScreen Queensland Sunshine Coast services

[figure not shown]

The results of our earlier qualitative studies^22^, ^23^ and experimental RCT^24^ — co‐designed with input from BreastScreen collaborators, as well as local and state community and BreastScreen Queensland panels that included Aboriginal and Torres Strait Islander women — informed the RCT study design and the additional information provided.

The breast density notification letter and additional breast density information will be given to women in arms 2 and 3 of the study with the mammography results report stating that their screening outcome was “no signs of breast cancer detected” (the Well Woman letters sent automatically to all women not recalled because of screen‐detected abnormalities). A short message outlining their breast density result and instructing women to refer to the additional information provided will be included in the Well Woman letters. Women will receive this information according to their pre‐specified information preferences from BreastScreen Queensland by post or via an SMS or email notification to access their results on the BreastScreen Queensland website.

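### The adjusted alpha of 0.013 does not match the three pairwise comparisons it is said to cover; the mismatch is conservative and minor

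*Protocol article*

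**What the plan says.** All the figures are in the Protocol article. Under Randomised controlled trial component of the study, the design has three arms: "Eligible women will be allocated in equal numbers to the three study arms". Three arms give exactly three pairs.

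Under Sample size calculation, the control proportion is set at 15% ("We assume that about 15% of women in the control group will report feeling anxious"), the target power is 80%, and the difference to be detected is "between each of the intervention arms and the control arm of ten percentage points". The significance level and the number it leads to are given as "adjusted α = 0.013 for three pairwise comparisons) would require that 373 women in each study arm". After retention of 80%, 70% and 70% at the three follow-ups, the recruitment target is 952 per arm, 2856 in all, so that 1119 remain at the end. The section closes by saying that family-wise error was not controlled beyond this.

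The article gives no overall alpha, adjustment method, sidedness or sample size formula. The Statistical analysis section names the model classes and no significance level.

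**The concern.** A per-comparison alpha adjusted for three comparisons should follow from the number three, and 0.013 does not do so by any of the usual routes from 0.05. Because 0.013 is the only multiplicity adjustment the article states, a reader judging the primary results will look to it. A p-value between 0.013 and 0.0167 would be classed differently depending on whether the number or its description governs.

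The protected family is also unclear. The power sentence concerns two contrasts (each intervention arm against control), the adjustment is described as covering three, and the number fits four. At stake are the clarity of the error control, a small amount of power, and the alpha from which the recruitment target was derived.

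**Working it through.** **Inputs.** From Sample size calculation: control proportion 0.15, difference 0.10, power 0.80, alpha 0.013, retention 0.80, 0.70 and 0.70. Allocation is equal across three arms. Assumptions, because the article does not state them: overall alpha 0.05, two-sided tests, and an increase from 15% to 25%. A fall to 5% does not reproduce the stated number (218 per arm at 0.013 with continuity correction).

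**Step 1: which number of comparisons gives 0.013?**
- Bonferroni, three: 0.05/3 = 0.0167
- Sidak, three: 1 − 0.95^(1/3) = 0.0170
- Tukey-type, all pairs of three arms: 0.0191
- Bonferroni, four: 0.05/4 = 0.0125, which rounds to 0.013
- Sidak, four: 1 − 0.95^(1/4) = 0.0127, which also rounds to 0.013

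None of the three-comparison values rounds to 0.013; both four-comparison values do.

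**Step 2: reproduce 373.** With p1 = 0.15, p2 = 0.25, mean p = 0.20 and d = 0.10:

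n = [z(α/2)·√(2·0.20·0.80) + z(β)·√(0.15·0.85 + 0.25·0.75)]² / d²

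Continuity-corrected: n′ = (n/4)·[1 + √(1 + 4/(n·d))]²

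At α = 0.013, z(α/2) = 2.484 and z(β) = 0.842:
- n = (2.484 × 0.5657 + 0.842 × 0.5612)² / 0.01 = 352.5, so 353
- n′ = 372.2, so **373**, as printed

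Attrition: 0.80 × 0.70 × 0.70 = 0.392. Then 373/0.392 = 951.5, so 952 per arm, and 3 × 952 = 2856. Also 3 × 373 = 1119. Every printed figure follows from 0.013.

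One caveat: without the continuity correction, α = 0.01 also gives 373. The article does not state 0.01, so the stated 0.013 with the correction is the natural reading.

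**Step 3: the same formula at other alphas.**

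| α | uncorrected | corrected | after ÷0.392 (corrected) |
|---|---|---|---|
| 0.0125 | 356 | 376 | not needed here |
| 0.013 | 353 | 373 | 952 per arm, 2856 total |
| 0.0167 | 334 | 354 | 904 per arm, 2712 total |

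The difference between 0.013 and 0.0167 is 19 per arm at the end of follow-up, and 2856 − 2712 = 144 women at recruitment.

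**Step 4: family-wise error over the three pairs.** From the studentized range distribution for three equal arms: 0.0347 at α = 0.013 and 0.0440 at α = 0.0167. The simple upper bound at 0.013 is 3 × 0.013 = 0.039.

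**Step 5: power, 15% versus 25%.** Uncorrected power is Φ{[d·√n − z(α/2)·0.5657]/0.5612}. Numbers per arm come from 952 and the retention figures applied in sequence.

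| Time | n per arm | α = 0.013 | α = 0.0167 | difference |
|---|---|---|---|---|
| 8 weeks | 952 × 0.80 = 761.6 | 99.2% | 99.4% | 0.2 points |
| 12 months | 761.6 × 0.70 = 533.1 | 94.6% | 95.6% | 0.9 points |
| 27 months | 373 | 82.6% | 84.8% | 2.2 points |

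The 12-month difference uses unrounded powers (0.9555 − 0.9464). With the continuity correction, n is replaced by (373 − 1/d)²/373 = 363²/373 = 353.3, and power at 27 months is 80.1% versus 82.5%.

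**The case against.** The strongest reply is that nothing is broken. The chain from 0.013 to 2856 is internally consistent, and a stricter per-comparison level than the family needs is permissible. The article does not state an overall 0.05 or a Bonferroni rule, so 0.0167 is a convention rather than a requirement. This stands as far as it goes. It does not remove the mismatch, because the article presents 0.013 as the adjustment for three comparisons, not as a deliberately stricter level, and gives no reasoning that leads from three to 0.013.

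A second reply is that the mislabelled item may be the number of comparisons rather than alpha. Two groups of primary outcomes, each tested for two intervention-versus-control contrasts, would make four and fit 0.0125. The article does not say this, and it conflicts with the words used, but it cannot be ruled out. The fix therefore has to leave both routes open.

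Two stronger readings are tempting and are not supported. A reader might infer that the sample size is inadequate; the opposite is true, since 354 would do where 373 are planned. A reader might also infer that 0.013 is the threshold for declaring results. The article uses it only as a planning input, and an analysis plan that is not shown may set the level, so any power lost in the analysis is conditional on 0.013 being carried forward.

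**Conclusion.** The point holds as a minor inconsistency. On an assumed overall two-sided 0.05, the stated alpha and the stated number of comparisons do not agree: 0.013 belongs to four comparisons, and only three are named. The sample size was built on 0.013.

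The effect is conservative. Family-wise error over three pairs is about 3.5% instead of 4.4%, and the planned number is 19 per arm above what 0.0167 would need. If 0.013 is used in the analysis, the power given up is about 2 points at 27 months and under 1 point at 8 weeks and 12 months. The time-point figures assume that retention multiplies across follow-ups, which is the reading that reproduces 952.

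No conclusion of the trial would become invalid. A three-arm closed test (a global test at 0.05, then pairs at 0.05) would use the error rate more fully, but its gain comes from a different procedure and is not a measure of this mismatch.

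**What to change.** Before analysis, make alpha and the number of comparisons agree, in the sample size section and wherever the analysis threshold is set. Only the authors know which family was meant, so either:

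- use 0.0167 for the three pairwise comparisons and restate power at 373 per arm as about 82-85% (82.5% continuity-corrected, 84.8% uncorrected); or
- keep 0.013 and correct the description to name the four comparisons it protects.

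In both cases state the overall alpha, the sidedness and the adjustment method in the same sentence. A three-arm closed test is an optional alternative. The cost is wording only; recruitment does not change.

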### Qualitative sub‐study component

Eight weeks after screening, we will purposively recruit (according to a range of socio‐demographic characteristics) sixty women (thirty from each of the two intervention study arms) for interviews by telephone or via Zoom that will be audio‐recorded and transcribed. The interviews will explore personal views regarding the RCT outcome measures over time, including feelings of anxiousness or confusion, interest in and reasons for seeking or not seeking supplemental screening, and the acceptability of breast density notification. The sample size is adequate for a qualitative study.^40^

The qualitative sub‐study will take a phenomenological perspective and the outcomes assessed using thematic analysis.^41^ This method enables themes to be compared both within individuals (eg, a woman's psychological response and understanding of breast density information, and her prior experience and future intentions regarding health service use) and between individuals (eg, women who are or are not anxious).

### Statistical analysis

We will summarise participant socio‐demographic and health characteristics as descriptive statistics (frequencies and proportions for categorical variables; means with standard deviations for continuous variables). Outcomes data by study arm will be analysed in linear mixed models and generalised linear mixed models; the regression models will take correlations between longitudinally collected data (when appropriate) and clustering by recruitment site into account, and allow inclusion of data from individuals for whom some longitudinal outcomes data are missing.

## Ethics approval

The Gold Coast Hospital and Health Service Ethics Committee (HREC/2023/QGC/8977) and Sunshine Coast Hospital and Health Service Research Governance and Development (SSA/2023/QSC/89770) have approved the study.

### Participant consent

Women will be informed in detail about the study prior to and on the day of their appointment, and will be provided a participant information statement and a consent form. The participant information statement will inform them about the aim and design of the study, and advise them that they may receive additional information about their breasts. The participant information statement does not mention the breast density criterion for study participation in order to ensure that participants in the control group are blinded to their breast density status. It will also include contact details for the research team and other support services, and state that participation is voluntary and without penalty should they not participate. Women will be informed that they will be contacted by SMS (or email if they do not have a mobile phone) with links to brief online questionnaires. They will also be informed that some personal information will be obtained from BreastScreen Queensland for study purposes only.

### Data safety

All data will be stored in password‐protected files on password‐protected computers, backed up to a University of Sydney server. Quantitative and qualitative study data will be retained for fifteen and five years, respectively, in accordance with National Health and Medical Research Council guidelines,^42^ after which the files will be deleted.

## Dissemination of findings

Evaluating the effects of notifying or not notifying women about dense breast information using two different modes of communicating will facilitate translation of our findings to BreastScreen Queensland and other screening services. They will be disseminated in publications in peer‐reviewed national and international journals, and presented at national and international conferences. Our findings will also be reported to BreastScreen Queensland, BreastScreen Australia, Cancer Australia, and other national and international bodies involved in cancer care and screening, including those currently considering routine notification of women about breast density and patient and support organisations.

No information that could identify study participants will be included in any presentation of our findings. All quantitative analyses will be of de‐identified data, and audio‐recordings and transcripts will be de‐identified for the qualitative sub‐study. Quantitative findings will be reported at the group level, and individual qualitative findings and quotes will be anonymised.

## Data sharing statement

In line with our ethics approval application, quantitative data will be anonymised and aggregated for statistical analyses, and findings will be reported at the group level. Qualitative findings will also be reported at the group level. Any additional unpublished aggregate‐level data will be available upon reasonable request at the conclusion of the RCT. Individual‐level data and RCT data files will not be accessible to external researchers.

## Trial registration

The RCT was prospectively registered with the Australian New Zealand Clinical Trials Registry on 9 January 2023 (ACTRN12623000001695p).

